# Pressure RElieving Support SUrfaces: a Randomised Evaluation 2 (PRESSURE 2): study protocol for a randomised controlled trial

**DOI:** 10.1186/s13063-016-1703-8

**Published:** 2016-12-20

**Keywords:** Pressure ulcers, Double triangular group sequential design, Randomised controlled trial, Alternating pressure mattress, Standard foam mattress, Quality of life

## Abstract

**Background:**

Pressure ulcers represent a major burden to patients, carers and the healthcare system, affecting approximately 1 in 17 hospital and 1 in 20 community patients. They impact greatly on an individual’s functional status and health-related quality of life. The mainstay of pressure ulcer prevention practice is the provision of pressure redistribution support surfaces and patient repositioning. The aim of the PRESSURE 2 study is to compare the two main mattress types utilised within the NHS: high-specification foam and alternating pressure mattresses, in the prevention of pressure ulcers.

**Methods/Design:**

PRESSURE 2 is a multicentre, open-label, randomised, double triangular, group sequential, parallel group trial. A maximum of 2954 ‘high-risk’ patients with evidence of acute illness will be randomised on a 1:1 basis to receive either a high-specification foam mattress or alternating-pressure mattress in conjunction with an electric profiling bed frame. The primary objective of the trial is to compare mattresses in terms of the time to developing a new Category 2 or above pressure ulcer by 30 days post end of treatment phase. Secondary endpoints include time to developing new Category 1 and 3 or above pressure ulcers, time to healing of pre-existing Category 2 pressure ulcers, health-related quality of life, cost-effectiveness, incidence of mattress change and safety. Validation objectives are to determine the responsiveness of the Pressure Ulcer Quality of Life-Prevention instrument and the feasibility of having a blinded endpoint assessment using photography. The trial will have a maximum of three planned analyses with unequally spaced reviews at event-driven coherent cut-points. The futility boundaries are constructed as non-binding to allow a decision for stopping early to be overruled by the Data Monitoring and Ethics Committee.

**Discussion:**

The double triangular, group sequential design of the PRESSURE 2 trial will provide an efficient design through the possibility of early stopping for demonstrating either superiority, inferiority of mattresses or futility of the trial. The trial optimises the potential for producing robust clinical evidence on the effectiveness of two commonly used mattresses in clinical practice earlier than in a conventional design.

**Trial registration:**

ISRCTN01151335. Registered on 14 May 2013. Protocol version: 5.0, dated 25 September 2015

Trial sponsor: [name], Faculty Head of Research Support, University of Leeds, [name]; [name]; [contact].

## Background

Pressure ulcers (PUs) represent a major burden to patients, carers and the healthcare system affecting approximately 1 in 17 hospital and 1 in 20 community patients [1–3]. They impact greatly on an individual’s functional status and health-related quality of life as a consequence of distressing symptoms including pain, exudate and odour, increased care burden, prolonged rehabilitation, requirement for bed rest, hospitalisation and for those who work, prolonged sickness absence [4, 5].

The primary cause of a PU is mechanical load in the form of pressure or pressure and shear, applied to soft tissues, generally over a bony prominence. They range in severity from non-blanchable erythema (Category 1), superficial skin loss (Category 2) to severe ulcers involving fat, muscle and bone (Category 3, 4 or unstageable) [6].

PU development is influenced by the intensity and duration of pressure and occurs when the soft tissues are unable to tolerate the sustained mechanical loads that develop between bony prominences and a support surface e.g. the sacrum and a mattress [7]. They are a cross-specialty problem, a complication of serious acute or chronic illness in patient populations characterised by high levels of co-morbidity and mortality [8, 9].

The mainstay of PU prevention practice is the provision of pressure redistribution support surfaces (mattresses, cushions) and patient repositioning, to minimise both the intensity and duration of pressure exposure of vulnerable skin sites, not adapted to sustained and/or excessive loading [6, 7]. Pressure-relieving mattresses either distribute the patient’s weight over a larger contact area providing ‘constant low pressure’ or they mechanically vary the pressure beneath the patient, so reducing the duration of the applied pressure [10].

The two main mattress types utilised within the National Health Service (NHS) are *high-specification foam* (HSF) mattresses, which are classified as a ‘low-tech constant low-pressure device’ and *alternating-pressure mattresses* (APMs), which are classified as ‘high-tech’ support surfaces [10, 11]. Alternating pressure mattresses are electrically powered and comprise large air-filled pockets which inflate and deflate in cycles.

The conclusions of the updated Cochrane systematic review [11] did not differ from the previous review [10]. The recent review concluded that foam alternatives to standard hospital foam mattresses reduce the incidence of pressure ulcers in patients at risk (RR 0.40 95% CI 0.21 to 0.74) [11]. One trial suggested that alternating-pressure mattresses may be more cost-effective than alternating-pressure overlays in a UK context [11]. However, the relative merits of APMs and constant low-pressure devices remain unclear and recommended the evaluation of APMs compared to constant low-pressure devices such as HSF [11].

There is evidence that some patients do not like APMs [12–14]. The alternating sensation is disliked by some patients and can cause feelings of nausea and impact upon sleep. In addition, upon patient movement, the air-filled pockets are compressed and patients find it difficult to mobilise in bed and also report feeling unstable at the mattress edge, either when they are getting in and out of bed or feeling like they will be ‘rolled out of bed’, creating an unsafe feeling [4, 12–14]. Other issues include noise from the pump, technical failure and attendant alarms.

The National Institute for Health and Care Excellence (NICE) guidance recommends the use of an HSF mattress in adults who are admitted to secondary care and who are assessed as being at high risk of developing a PU in primary and community care settings [7]. HSF mattresses are also recommended for adults with a PU, and if this is not sufficient to re-distribute pressure, to consider the use of a dynamic support surface [7]. Therefore the NICE guidance states that HSF is the recommended ‘minimum’ standard of care for mattress provision in the prevention and treatment of PUs. Despite the large difference in the unit cost with HSF units ranging from £180 to £600 and APM units ranging from £1000 to £5000 and limited evidence of benefit of APMs compared to HSF in PU prevention, they are in widespread clinical use. This has been evidenced in the National Institute of Health Research (NIHR) PURPOSE pain cohort study where mattress allocation by ward staff to a high-risk target population (mobility impaired and/or Category 1 PU and/or pressure area-related pain) was 48% HSF: 52% APM [15, 16], reflecting a lack of standardised practice and clinical uncertainty relating to mattress provision for ‘high-risk’ patients.

In light of the priority being given to PU prevention by the NHS [7], the high cost and lack of evidence relating to the effectiveness of mattresses in common use in the NHS, ad hoc practice in mattress allocation and the disadvantages and difficulties reported by patients in the use of APMs, we are undertaking a randomised controlled trial (RCT) to compare HSF and APMs in a high-risk in-patient population.

### Objectives

The main aim of the study is to determine the clinical and cost effectiveness of high-specification foam (HSF) and alternating-pressure mattresses (APM) when both are used in conjunction with an electric profiling bed frame in secondary care and community in-patients facilities in patients with evidence of acute illness, for the prevention of Category 2 (and above) PU.

The primary objective is to compare the time to developing a new Category 2 or above PU, in patients using HSF to those using APM by 30 days post end of treatment phase.

The secondary objectives are:To compare the time to developing a new Category 3 or above PU, between patients using HSF and those using APMTo compare the time to developing a new Category 1 or above PU, between patients using HSF and those using APMTo compare the time to healing of pre-existing Category 2 PU between patients using HSF and those using APMTo determine the impact of HSF and APM on health-related quality of lifeTo determine the incremental cost-effectiveness of APM compared to HSF from the perspective of the health and social care sectorsTo compare incidence of mattress change between patients using HSF and those using APMTo compare safety between patients using HSF and those using APM

### Secondary validation objectives

To determine responsiveness of the Pressure Ulcer Quality of Life-Prevention (PU-QoL-P) instrumentTo assess the feasibility of a blinded outcome assessment using photography and central blinded endpoint review

## Methods/Design

The PRESSURE 2 trial is a multicentre, open, randomised, double triangular group sequential, parallel group trial, with two planned interim analyses and validation substudies.

A maximum of 2954 ‘high-risk’ patients with evidence of acute illness will be randomised to receive either HSF or APM in conjunction with an electric profiling bed frame from randomisation to the end of the treatment phase (maximum 60 days), with a final assessment at 30 days post the end of treatment phase (Fig 1).

**Fig. 1 Fig1:**
[figure not shown]
Trial flow diagram

### Study population

The multicentre trial will be conducted in acute secondary care hospitals, community hospitals and NHS-funded intermediate care/rehabilitation facilities in England and Scotland. All participating centres have Tissue Viability Nurse Specialists in post with hospital-wide remits to establish pressure ulcer prevention guidelines, policies and practice. Patients with evidence of acute illness will be assessed for eligibility in accordance with the criteria in Table 1.

**Table 1 Tab1:** Inclusion and exclusion criteria

Inclusion criteria
1. Evidence of acute illness through:
a. acute admission to secondary care hospital, community hospital or NHS-funded intermediate care/rehabilitation facility
b. secondary care, community hospital or NHS-funded intermediate care/rehabilitation facility in-patient with onset of acute illness secondary to elective admission
c. recent secondary care hospital discharge to community hospital or NHS-funded intermediate care/rehabilitation facility
2. Aged ≥ 18 years
3. Have an expected total length of stay of 5 or more days
4. At high risk of PU development due to one or more of the following:
a. bedfast/chairfast AND completely immobile/very limited mobility (Braden activity score 1 or 2 and Mobility score 1 or 2) [20]
b. Category 1 PU on any pressure area skin site
c. localised skin pain on a healthy, altered or Category 1 pressure area skin site
5. Consent to participate (written informed consent, witnessed verbal consent, consultee agreement (England) or nearest relative/guardian/welfare attorney (Scotland))
6. Expected to comply with the follow-up schedule
7. The patient is on an electric profiling bed frame
Exclusion criteria
1. Have previously participated in the PRESSURE 2 trial
2. Have a current or previous Category ≥3 PU
3. Have planned admission to ICU where standard care is alternating-pressure mattress provision
4. Unable to receive the intervention (for example, sleep at night in a chair or unable to be transferred to randomised mattress)
5. Patient weight is lower or higher than weight limits for HSF and alternating-pressure mattresses (<45 kg/>180 kg)
6. It is ethically inappropriate to approach the patient

*HSF* high-specification foam, *ICU* intensive care unit, *NHS* National Health Service, *PU* pressure ulcer

## Consent

Where eligibility is indicated by the attending clinical team, patients will be flagged to a member of the hospital Tissue Viability Team (TVT). A full verbal explanation of the study Patient Information Leaflet (PIL) will be provided by a member of the TVT for the patient to consider. Following information provision, patients will have as long as they need to consider participation and will be given the opportunity to discuss the study with their family and other healthcare professionals before they are asked whether they would be willing to participate in the study. Assenting patients will be formally assessed for eligibility and invited to provide informed consent.

For patients capable of giving consent but physically unable to complete the written aspects of the consent form, witnessed consent will be provided by a family member or friend of the patient, or another member of the patient’s healthcare team who is not directly involved in the research study using the Witnessed Consent Form.

A large proportion of patients at risk of pressure ulcers have cognitive impairment affecting their understanding of the trial and/or dementia. Cognition impacts upon compliance with repositioning and self-care in the use of the electric profiling functionality, which is an integral component of the intervention package. It is important that the trial population is representative of the normal NHS patient population and therefore patients who lack capacity will also be recruited onto the trial.

The assessment of capacity will relate specifically to decisions pertaining to this particular research project. Each patient will be assumed to have capacity unless it is established that they lack capacity. Ward-based nurses identifying patients for study participation will be asked to consider aspects of capacity before any approach to patients is made and during the information-giving stage prior to consent. The TVT member will assess the patient’s ability to understand what decisions they need to make and why; the consequences of the decision to participate; their ability to understand, use and retain the information related to the decision to participate and be able to communicate their decisions effectively (as specified in the Mental Capacity Act 2005). If there is any concern about capacity the ward nurse/TVT member will consult further with other members of the attending clinical team and/or relative/carer/friend (as appropriate) and a decision will be made with the relative/carer/friend as to whether the patient is able to provide written consent. Where the patient is thought not to have capacity to consent, a relative, carer or friend who is interested in the patient’s welfare will act as a personal consultee or nearest relative/guardian/welfare attorney (Scotland).

The relative/carer/friend will be involved in the information and decision-making process with the patient and will advise the TVT member on their presumed wishes and feelings and consultee or nearest relative/guardian/welfare attorney (Scotland) assent will be obtained on behalf of the patient. The relative, carer or friend will be advised to set aside their own views and provide advice on the participation of the patient in the research, taking into consideration the patient’s wishes and interests. Patients will not be required to do anything which is contrary to any advance decisions or statements that have been made by them in relation to their treatment or any other matter. Advance decisions made by the patient about their preferences and wishes will always take precedence.

If, despite taking all reasonable steps, a personal consultee cannot be identified and contacted then a nominated consultee or nearest relative/guardian/welfare attorney (Scotland) would be approached. This person would have no connection with the research project. They would be nominated by the TVT member; they would most likely be the patient’s lead clinician. The consultee or nearest relative/guardian/welfare attorney (Scotland) would be provided with the information leaflet describing the research study and the role of the consultee/nearest relative/guardian/welfare attorney and it would be emphasised that they are being asked to act on behalf of the patient, rather than on any personal views or feelings.

Where a patient has been enrolled into the study after consultee or nearest relative/guardian/welfare attorney (Scotland) agreement and they subsequently regain capacity, a member of the research team will discuss the study with the patient; provide a full verbal explanation of the trial and a Patient Information Leaflet explaining the trial and their participation in the trial. Assenting patients will be invited to provide informed consent/witnessed verbal consent for ongoing participation. Those who do not wish to continue in the trial will be withdrawn.

Consent for photographs to be taken of skin sites will be obtained at time of consent to the trial with an opt-out clause allowing patients to withdraw consent for photographs at any time.

Patients who change from their allocated mattress will continue follow-up assessments unless they are unwilling to do so, and patients who withdraw from the trial will continue to be managed in line with standard care. Patients with capacity at study entry who subsequently lose capacity will be withdrawn from the trial.

## Randomisation

Following confirmation of informed consent, eligibility and completion of baseline assessments, patients will be randomised by an authorised member of the research team at the site. Patients will be randomised in a 1:1 allocation ratio, to receive either HSF or APM. Randomisation will be performed using minimisation, incorporating a random element, via a central 24-hour automated telephone randomisation system based at the Leeds Institute of Clinical Trials Research (LICTR). The dynamic allocation method should ensure intervention groups are well balanced for the following minimisation/stratification factors:CentrePU status (no pressure ulcer, Category 1, Category 2)Secondary care hospital, community hospital, intermediate care or rehabilitation facilityMethod of consent (written OR witnessed verbal OR consultee or nearest relative/guardian/welfare attorney (Scotland) agreement)

The randomisation system will include an automated internal check using NHS numbers to confirm that the patient has not been recruited to the trial previously.

In addition, at the time of randomisation, 10% of patients will be randomly selected for expert clinical assessment and photography.

## Interventions

Patients will be randomised to either HSF or APM products used by the participating centre.

Specifications for both HSF and APM have been developed and mattresses are approved for inclusion in the trial based on these specifications, as defined in a PRESSURE 2 Mattress Specification Guideline. The guideline for HSF includes foam density (foam fatigue and foam hardness) and mattress cover characteristics (removable, minimum two-way stretch, vapour-permeable, covered zips) as defined in BS 3379 [17] and for APMs includes minimum and maximum values for cell height, cycle time and cycle frequency [17]. All mattresses will comply with the Medical Devices Regulations SI2002/618. The PRESSURE 2 Mattress Specification Guideline also provides details of excluded mattresses including: low air loss mattresses; combination mattresses e.g. static foam and alternating cells, static foam and gel, hybrid alternating and low air loss; and other continuous static low-pressure mattresses including fibregel, fluid and air filled mattresses.

Trial-approved mattresses are identified at each centre on an ongoing basis. After randomisation an eligible mattress will be sourced and allocated by the Clinical Research Nurse (CRN)/Registered Healthcare Professional (RHCP). Mattress allocation is expected within 24 hours of randomisation.

All patients will have an electric profiling bed frame as an adjunct to the trial mattress.

## Assessments/data collection and follow-up

### Baseline assessment

Patient demographic information including NHS number, date of birth, gender, date of admission, type of admission, category of medical condition (orthopaedics and trauma, oncology, critical care and other conditions) and ethnicity will be recorded.

Patient risk profiles and key risk factors will be recorded through clinical assessment and completion of the Braden scale and PURPOSE-T including baseline skin status, localised skin pain on pressure areas, activity and mobility status, sensory perception, diabetes, conditions affecting macro and micro circulatory function, nutrition, skin moisture, friction and shear, PU history, height and weight (self-report or notes where available) and duration and size of ulcer and photograph (if consented) for patients with a pre-existing category 2 PU [9, 15, 16, 18].

PU prevention interventions pre-randomisation will be recorded including mattress type, turning frequency and seating provision.

Patients will be asked to complete quality of life questionnaires, which include: 12-item Short Form (SF-12), Pressure Ulcer Quality of Life-Utility Index (PUQoL-UI) [15] and EuroQol-5D 5 level (EQ-5D-5L); with the latter two by proxy for patients who lack capacity. In addition PUQoL-Prevention (P) data, an adapted version of PUQoL [19], will be collected in a subset of patients.

It is expected that the baseline assessment and randomisation will take place on the same day.

### Treatment phase follow-up assessment

Treatment phase follow-up assessments will be undertaken up to a maximum of 60 days post randomisation. These will be undertaken by a trained CRN/RHCP twice weekly from randomisation up to 30 days, then once weekly up to 60 days. The treatment phase is defined as the period from randomisation to discharge, transfer to an ineligible facility, when the patient is considered no longer at high risk (considered at each assessment), reaching 60 days, withdrawal or death, whichever is soonest. No longer at high risk is defined as no Category 1 or above PU on any skin site AND no localised skin pain on a healthy, altered or Category 1 skin site, AND improved mobility and activity (Braden activity score 3 or 4 AND Mobility score 3 or 4) [20].

Patients will have a skin assessment, including pain and photography (if consented) of Category 2 and above ulcers where present and not previously photographed, and PU prevention interventions recorded. Mattress compliance and technical faults will be collected daily. At weeks 1 and 3 post randomisation*,* healthcare resource utilisation, and quality of life questionnaires SF-12 [21], PUQoL-UI and EQ-5D-5L [22] will be completed (PUQoL-UI and EQ-5D-5L by proxy for patients lacking consent); the PU-QoL-P will again be administered to a subset of patients.

Following the end of the treatment phase patients will receive care in line with routine standard practice.

### Post-treatment phase follow-up assessment

At 30 days post end of the treatment phase, a final skin assessment (including photography if selected) will be undertaken at the patient’s home or care facility by a member of the research team. This assessment will only be at 90 days if the end of the treatment phase has a duration of 60 days. Should the patient be discharged, considered as no longer at high risk, or transferred to an ineligible facility prior to 90 days then the final follow-up assessment will be scheduled to take place at 30 days post the date of: discharge, no longer at risk or transfer.

Healthcare resource utilisation, and quality of life questionnaires (SF-12, Pressure Ulcer Quality of Life-Utility Index (PUQOL-UI) and EQ-5D-5L; and PU-QoL-P in a subset of patients) will be completed.

See Fig. 2, for the schedule of enrolment, interventions, and assessments.

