## Endpoints

### Primary endpoint

The primary endpoint is time to developing a new Category 2 or above PU from randomisation to 30 days from the end of the treatment phase (maximum of 90 days).

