### Primary endpoint analysis

#### Primary analysis

A Cox proportional hazards model (after confirming the proportional hazards assumption is valid) will be fitted to the primary endpoint, with adjustment for the minimisation factors: healthcare setting, PU status and consent, and the following covariates: presence of pain on a healthy, altered or Category 1 PU skin site, conditions affecting peripheral circulation and treatment group. Centre will be assessed for inclusion as a random effect. The hazard ratio for the estimate of the treatment effect and adjusted confidence interval corresponding to the nominal *p* value will be presented. Patients who do not develop a Category 2 or above PU during the treatment phase or by 30 days post treatment follow-up will be censored at the date of their last evaluable skin assessment.

Kaplan-Meier estimates of the probability of patients developing a Category 2 or above PU over 90 days in each group and adjusted confidence intervals corresponding to the nominal *p* value will be presented.

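### The final-visit rule is triggered by discharge or transfer up to day 90 instead of day 60, so read literally it can put the last skin check on days 91 to 119, after the 90-day primary endpoint window closes

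*Protocol article*

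**What the plan says.** All references are to the protocol article.

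- **Methods/Design** describes allocation until the "end of the treatment phase (maximum 60 days), with a final assessment at 30 days post the end of treatment phase".
- **Treatment phase follow-up assessment** has the same limit: "Treatment phase follow-up assessments will be undertaken up to a maximum of 60 days post randomisation". The phase closes at the first of discharge, transfer to an ineligible facility, no longer being at high risk, "reaching 60 days, withdrawal or death, whichever is soonest".
- **Post-treatment phase follow-up assessment** opens with the general rule: "At 30 days post end of the treatment phase, a final skin assessment". It then adds: "This assessment will only be at 90 days if the end of the treatment phase has a duration of 60 days".
- **The next sentence of that section** covers discharge and loss of high risk together with patients "transferred to an ineligible facility prior to 90 days then the final follow-up assessment will be scheduled to take place at 30 days post", where the 30 days are counted from that event.
- **Primary endpoint** runs "from randomisation to 30 days from the end of the treatment phase (maximum of 90 days").
- **Primary analysis** says that patients without a new Category 2 or above ulcer "will be censored at the date of their last evaluable skin assessment". It reports Kaplan-Meier estimates over 90 days.

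**The concern.** Every other statement ties the final visit to the end of the treatment phase, which cannot fall after day 60. The sentence on discharge and transfer ties it to the event itself, for any event before day 90. A discharge on day 75 cannot end a treatment phase that closed on day 60, yet on its plain wording this sentence resets the visit.

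Scheduled treatment-phase skin checks stop at day 60, so for a patient who reaches day 60 the final visit is the only later scheduled observation of the primary endpoint. If it takes place after day 90, an ulcer first recorded there may have begun before or after the window closed. The censoring rule refers to the last evaluable assessment and gives no cut at day 90, so the article does not say how such an ulcer, or such a follow-up time, enters the analysis.

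**Working it through.** **Inputs**

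- Latest end of treatment phase: day 60 (Methods/Design; Treatment phase follow-up assessment).
- Interval from end of treatment to final visit: 30 days (Post-treatment phase follow-up assessment).
- Trigger limit in the discharge and transfer sentence: before day 90 (same section).
- Endpoint maximum: 90 days (Primary endpoint).

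**Step 1: reproduce the plan's own maximum.** Let d be the day of discharge or transfer. Under the general rule,

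final visit = min(d, 60) + 30.

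The largest value is 60 + 30 = 90. This matches the stated endpoint maximum and the Kaplan-Meier horizon.

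**Step 2: apply the discharge and transfer sentence as written.** For every d below 90,

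final visit = d + 30.

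**Step 3: compare the two rules.**

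| Event day d | General rule | Sentence as written | Days past day 90 |
|---|---|---|---|
| 45 | 75 | 75 | 0 |
| 59 | 89 | 89 | 0 |
| 60 | 90 | 90 | 0 |
| 61 | 90 | 91 | 1 |
| 75 | 90 | 105 | 15 |
| 89 | 90 | 119 | 29 |

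The rules agree up to day 60. They conflict on each of the 29 event days from 61 to 89, by d − 60 days, so by 1 to 29 days.

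**Step 4: what this does to the dating of an ulcer.** Suppose the last clear skin check was on day 60 and an ulcer is first seen at the final visit. At a day-90 visit, onset lies in a 30-day interval wholly inside the window. At a visit on day d + 30 the interval is d − 30 days long, of which 30 days lie inside the window and d − 60 outside:

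- d = 61: 31 days, 1 outside.
- d = 75: 45 days, 15 outside.
- d = 89: 59 days, 29 outside.

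An ulcer-free late visit does not raise this problem. It covers the window up to day 90, and only the censoring date exceeds the stated maximum.

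**Step 5: check the correction.** If the sentence covers only events before day 60, the latest visit that it can produce is 59 + 30 = day 89. Patients who complete 60 days are seen on day 90, and no scheduled visit falls outside the window.

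**The case against.** The strongest reply is that this is a slip that nobody would follow. The general rule appears consistently in the abstract, the objectives, Methods/Design, the opening of the section itself and the endpoint definition. The disputed sentence lists three of the events that end the treatment phase, and it comes straight after the statement on when the visit falls at day 90. In context it seems meant to say that patients who leave treatment early are seen earlier than day 90. The schedule figure and the full protocol are not shown, so it cannot be established that any site worked to the literal wording. Much of this stands: a slip is the likely explanation, and many readers would let the general rule prevail. However, the article does not say that it prevails, and the sentence is a scheduling instruction with a stated day that contradicts its neighbours. That is more than a detail left to the full protocol.

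Three stronger readings are tempting, and the documents do not support them.

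- **That many patients are affected.** The article gives no length-of-stay distribution, only an expected stay of 5 or more days for eligibility. The group is limited to patients still in an eligible facility and at high risk on day 60, without a primary event, who then leave before day 90. Loss of high risk adds little, because that status is considered at treatment-phase assessments, which stop by day 60.
- **That the last 30 days of the endpoint are lost for all of them.** An ulcer-free late visit loses no information on the window. Only a positive finding at that visit is ambiguous. The Discussion also expects ulcers to develop quickly, with later ones in a minority of patients.
- **That the comparison is biased between mattresses.** That would need discharge or transfer after day 60 to differ by arm, and nothing in the article suggests that it does.

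**Conclusion.** The contradiction is real on the face of the text. For discharge or transfer on days 61 to 89, one rule gives day 90 and the other gives days 91 to 119, up to 29 days beyond the stated endpoint maximum. The consequence is confined to ulcers first seen at such a late visit. They cannot be assigned to the primary window, and the analysis section as given does not settle how to treat them.

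This rests on reading the sentence literally, and on the final visit being the only scheduled skin check after day 60, as the article describes. The number of patients is not given and is probably small. No sample-size or event figure changes, and no effect on the treatment comparison is demonstrated. It is an inconsistency in the timing of the primary endpoint that should be corrected, and it does not call the design into question.

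**What to change.** Reconcile the sections Treatment phase follow-up assessment, Post-treatment phase follow-up assessment and Primary endpoint:

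1. Limit the discharge and transfer sentence to events that end the treatment phase, that is, before day 60.
2. State that discharge or transfer after day 60 does not move the day-90 assessment.

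The cost is a short text correction and a reminder to sites. It adds no visits and leaves the sample size and the analysis model unchanged.
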